### 10.4 Responsibilities

The SLT checks for unexpected increases of stuttering or long-term plateauing of severe or moderate stuttering when PCWS attend for treatment and/or maintenance. They ensure these events are recorded in REDCap.

The Trial Statistician reviews periodically unblinded overall safety data to determine patterns and trends of events, or to identify safety issues, which are not apparent on an individual case basis.

The CI has a clinical overview of the safety of the PCWS participating in the trial, including an ongoing review of the risk/benefit.

The Trial Management Group collects data centrally and evaluates the adverse event according to the trial protocol. The group takes a decision for action to mitigate the adverse event.

The Co-Cis follow up with the SLTs on the actions that need to be taken and report back to the Trial Management Group meeting.

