## **8.4 Blinding**

The participating SLTs, PCWS and their parents are not blinded to the treatment approaches that they deliver/receive. The three treatment approaches (Mini-KIDS, SCBT and the LP) use distinct techniques. Blinding is thus impossible.

The video analysts who are scoring %SS and SR are blinded to the treatment approaches that the PCWS receives. In the unlikely event that a video analyst is unblinded for the treatment that is delivered by the SLT in a video, for example if the video analyst recognises the name of a PCWS in the video because it was mentioned by the SLT during a SLT-RCT committee meeting, the video analyst will stop rating the video and will transfer the video to another video analyst who is blinded to the treatment.

Two video analysts are not blinded and will assess the French and Dutch video recordings for treatment fidelity.

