### 8.7.4 *If randomised in the LP*

If a situation indicates so, additional instruments to the ones administered during the baseline session could be used to identify comorbid disorders. The 10-point stuttering rating scale (Onslow et al., 2021) is introduced to the parents to record daily severity ratings of the PCWS' typical stuttering throughout the day. The scale scores include 0 = for no stuttering, 1 = for extremely mild stuttering and 9 = for extremely severe stuttering. A stuttering severity chart is provided to record the daily scores (at the end of each day).

The baseline session for the PCWS who receives the LP takes 1 hour 30 minutes, except if additional instruments are administered for comorbidities but are meant to individualise the treatment.

Results from the additional instruments are not recorded in the eCRF.

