#### **8.8.5 3-months post-randomisation data collection point**

One week before the 3-month post-randomisation data collection point, the SLT receives an automatic alert that the 3-month data collection point approaches so the SLT can prepare the session.

At the session + or – 2 weeks the 3-months post-randomisation data collection point, the SLT video records a speech sample from the PCWS with the parent and/or the SLT at the beginning of the treatment session. The SLT loads this onto a GDPR-proof platform.

Like for each treatment session, the SLT checks for treatment compliance and treatment fidelity, based on the treatment arm. The description of this procedure is described below. The checklists are added in Appendix 9. The SLT reports any risks.

The parent is asked to video record a conversation with the PCWS at home. The SLT loads this a GDPR-proof platform and labels the video recording according to the requirements. No treatment is provided during this conversation. The instructions for the video recording need to be followed.

The parent is also asked to complete the EQ-5D-Y proxy 1 and the ISPP-questionnaire on an electronic device (computer or smart phone) within a fortnight. The parent is also asked to report on their child's stuttering severity based on a 10-point scale with three descriptors only and to report on the satisfaction of the PCWS's communication in everyday speaking situations based on a 9-point scale with two descriptors only. This will be automatically scheduled using REDCap and access to the questionnaires is emailed to the parent. The SLT checks in REDCap if the questionnaires were completed by the parent.

The SLT also ascertains that the information about the treatment sessions that were scheduled between the baseline and the 3-month data collection point is uploaded in REDCap: the date and duration of each session and the information of the compliance check and treatment fidelity checklist of each session.

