# **10 SAFETY RECORDING AND REPORTING**

## 10.1 Definitions

Adverse events in this trial are unlikely to occur but may include a significant increase (e.g.,  $\geq 5\%$ SS) of the stuttering compared to baseline measures or a long-term lack of reduction of moderate or severe stuttering (e.g., for 10 weeks).

Serious adverse events, such as the death of a PCWS, are extremely unlikely to be linked to this TreatPaCS as the treatment approaches have no life-threatening consequences.

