## 10.2 Recording of safety findings in function of the available evidence

### 10.2.1 *The case of types of intervention that are in routine clinical use*

Increased stuttering indicates that the treatment is not effective. It may harm a PCWS to stutter for a significant amount of time with increased stuttering compared to the baseline stuttering severity (e.g.,  $\geq 5\%$ SS versus the %SS measured by the blinded video analysts in the video recordings of the baseline session) or to have no reduction of the moderate or severe stuttering compared to the baseline session (e.g., over a period of 10 weeks). As a PCWS's awareness about stuttering increases with age, the opportunity to receive treatment that can decrease stuttering successfully decreases with age and a PCWS may develop feelings of anxiety associated with the stuttering if the stuttering persists. Therefore, it is necessary to act when an adverse event is reported.

Mini-KIDS and SCBT are the experimental interventions in this trial. Even though they are not evidence-based as a treatment in their whole, they are practise-based given they are routinely delivered in daily practice. The techniques and procedures that are used in both treatments are evidence-based on their own. Therefore, possible adverse events are known and are limited to the ones listed previously.

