- For the continuous measures SR, EQ-5D-Y proxy 1, measured at different time points we can compare the evolution over time between the programs using a linear mixed model. This model also allows to look at differences at a specific time point in a post-hoc comparison. For the answers to the ISPP-questionnaire measured at different time points this can be done using a generalized linear mixed model. For the ordinal outcomes parent report about their PCWS's stuttering severity and their satisfaction about the PCWS's communication in everyday speaking situations depending on variability a linear mixed or generalized linear mixed model will be used.
- The number of weeks, the number of treatment sessions, the treatment time needed until the maintenance phase begins will be compared between the three programs using an ANOVA or Kruskal Wallis test as appropriate. This outcome will also be studied in a multiple linear regression model adjusting for possible confounders.
- We will look at the proportion of children that are successful (defined as  $<1\%$  SS and  $SR \leq 1$ ) at 18 months and at 5 years post-randomisation. They will be compared by a Chi-square test (or Fisher's exact test as appropriate) between the three programs. The time to reach success between the three programs will be compared with a Kaplan-Meier plot and analyzed using a Cox regression model with correction for confounders.
- %SS and SR at 18 months post-randomisation will be evaluated separately for the videos at home and for the videos recorded during the treatment sessions using linear regression models as described for the averages of the two samples.
- For the above analysis we will first consider the intention-to-treat population to preserve randomization, if necessary also per-protocol population will be considered.
- Safety analysis will be done in all patients that are randomised.
- Numbers of children who drop out and reasons for drop out, as well as leave the allocated treatment arm (numbers, reason and switched treatment) will be described per treatment. Numbers per program will be compared using a Chi-square test (or Fisher's exact test as appropriate). A time to drop-out analysis or a time to switch analysis will be performed in case  $> 10\%$  drop-out or a 10% switch was present in the trial.

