**Lidcombe Program**

**Date treatment session:** ...../...../.....

**Duration of the treatment session:** 30 / 60 / ..... minutes

Implementation of the treatment at home was

OR ☐ an agreed practice time at home and lasted ..... minutes. It was performed ... times since the previous treatment session

AND/OR ☐ applying a technique or advice throughout the day

☐ At least one parent attends the treatment session with the child

☐ The parent brings the severity ratings for the typical stuttering severity observed each day (outside of the practice conversations) since the previous treatment session

☐ The parent manages the treatment activity while remaining focused on the child's speech

☐ The parent identifies stuttering moments and only gives verbal contingencies for unambiguous stuttering or unambiguous stutter-free speech

☐ The parent gives verbal contingencies:

☐ correctly (in an immediate, accurate, genuine and positive way that does not disrupt the parent-child communication)

☐ mostly for stutter-free speech

☐ in a varied way regarding the wording, timing, and context

☐ frequently enough

☐ without negative reaction from the child

☐ The child is fluent most of the time during the practice sessions at home

☐ The parent implemented verbal contingencies at home during practice sessions during 10 to 15 minutes or during natural conversations.

☐ The verbal contingencies were only given by the parent who is trained to do so

**Treatment Fidelity Checklist** *(to check whether SLTs are implementing the treatment per protocol)*

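### The plateau adverse event has no named measure and only the LP arm must keep frequent severity ratings, so raw therapist-reported counts are not comparable between arms

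*Protocol*

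**What the plan says.** Protocol section 10.1 gives two examples of adverse events. One is a marked rise in stuttering. The other is "a long-term lack of reduction of moderate or severe stuttering (e.g., for 10 weeks". Section 10.2.1 adds the reference point: "no reduction of the moderate or severe stuttering compared to the baseline session (e.g., over a period of 10 weeks". For the rise, 10.2.1 names a measure, %SS as scored by the blinded video analysts. For the plateau it names none, and neither does 10.3.

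Detection is assigned in section 10.4, in the same words for all arms: "The SLT checks for unexpected increases of stuttering or long-term plateauing of severe or moderate stuttering when PCWS attend for treatment and/or maintenance". Section 8.4 states: "The participating SLTs, PCWS and their parents are not blinded to the treatment approaches that they deliver/receive".

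What the SLT must have to hand differs by arm:

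- **LP.** Under 8.7.4 a 10-point scale "is introduced to the parents to record daily severity ratings of the PCWS' typical stuttering throughout the day". The Appendix 9 compliance checklist includes the item "The parent brings the severity ratings for the typical stuttering severity observed each day". Section 9.3.1 has the SLT record a severity rating (SR) at each Stage 1 session, and the fidelity checklist has the SLT discuss the parent's ratings.
- **Mini-KIDS.** The Appendix 9 checklists mention observation forms of unspecified content. They contain no severity rating.
- **SCBT.** The Appendix 9 checklists contain no severity rating. The exit criterion in 9.1.5 requires reduced severity over 3 to 4 months but names no instrument.

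Section 8.8.3 sets weekly sessions, twice weekly in SCBT. In every arm parents are asked at the scheduled points to "report on their child's stuttering severity based on a 10-point scale with three descriptors only" (quoted from 8.8.5), and two videos are taken for blinded %SS and SR. Neither measure is linked to adverse event detection. On analysis, 11.3.3 says "Safety analysis will be done in all patients that are randomised", and 10.4 adds a periodic review by the trial statistician for patterns and trends.

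**The concern.** An event without a defined measure is found according to what the observer happens to have. Here the observer is unblinded, is required to hold a dense numeric record in one arm only, and sees children at different frequencies by arm. Two children with the same course could be recorded differently because of the programme they were assigned to.

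Two things are at stake. The periodic trend review and any by-arm adverse event table would mix true differences with differences in ascertainment. And a report is what sets action in motion: under 10.2.2, 10.3 and 10.7 the Trial Management Group may individualise treatment or decide that the child leaves the arm or the study. A plateau that nobody recognises does not reach that group. Unequal reporting could also carry over into the numbers leaving the allocated arm, which 11.3.3 compares between programmes, though the protocol gives nothing from which to size that.

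**Working it through.** The protocol states no figure for this event, so there is none to reproduce. The check sets the arms side by side and counts the opportunities for detection.

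**Required observations in a 10-week window during active treatment** (sections 8.7.4, 8.8.3, 9.1 to 9.3, Appendix 9)

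| | LP | Mini-KIDS | SCBT |
|---|---|---|---|
| Sessions | 10 × 1 = 10 | 10 × 1 = 10 | 10 × 2 = 20 |
| Daily parent ratings | 10 × 7 = 70 | none required | none required |
| SR at each session | about 10 | none required | none required |
| Observer blinded? | no | no | no |

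The LP figures are maxima under full adherence. They apply to Stage 1, which is where a child without reduction would be: moving to Stage 2 requires ratings of 0 and 1. In the maintenance phase all arms share the same checklists, without severity ratings.

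**Measures common to all arms** (8.8.3 to 8.8.9, Figure 3)

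The parent rating and the blinded %SS and SR are collected at baseline and at 3, 6, 9, 12 and 18 months. One month is 52.18/12 = 4.35 weeks, and each follow-up point has a window of ±2 weeks.

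- Baseline to month 3: 3 × 4.35 = 13.0 weeks, so 11 to 15 weeks.
- Each later 3-month gap: 13.0 ± 4, so 9 to 17 weeks.
- Months 12 to 18: 6 × 4.35 = 26.1 weeks, so about 22 to 30 weeks.

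A child with no reduction from baseline can therefore be identified with the same tool in every arm at week 11 to 15, but not at week 10.

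**Timing of the blinded scores.** Section 8.9.3 starts video analysis 6 months after recruitment begins, and 8.8.3 and 8.8.9 have the scores assigned later. They can support an unbiased table but not a timely alert. The parent rating, held in REDCap (12.1), is available promptly.

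**Direction.** Dense ratings could raise detection in LP. Twice the number of sessions could raise it in SCBT. The documents do not show which dominates.

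**The case against.** The strongest reply is that 10.4 gives one check, in identical words, for every arm. No section says that LP events are declared from the daily ratings, which are described as part of the treatment, and the LP therapist is just as unblinded as the others. A reader might infer that LP events are detected from the chart and the others from impression; the text does not establish that. What stands is narrower: only in LP is the SLT required to have such ratings.

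Safeguards common to all arms also exist. The SLT reports any risks at 3, 6, 9, 12 and 18 months (8.8.5 to 8.8.9), and Figure 3 schedules a risk assessment at those points and at 2 years. SCBT exit and the Mini-KIDS stage goals oblige the SLT to follow severity, and participating SLTs have at least 2 years' experience (section 6). These reduce the chance that a plateau goes unnoticed, but they supply no common measure.

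The safety flow chart (Appendix 11) is a figure that is not shown. The safety reporting checklist, the risk management plan and the treatment guides are separate documents, and any SAP was not available. If one of them fixes a measure for all arms, the point reduces to a missing cross-reference.

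Finally, 11.3.3 states no between-arm test of adverse events. Its Chi-square test concerns drop-out and switching.

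**Conclusion.** The point holds in a limited form. The visible protocol names no measure for the plateau event and gives detection to an unblinded therapist. It equips that therapist with required daily and per-session ratings only in LP, and contact frequency differs as well. Raw SLT-reported counts are therefore not comparable between arms without a common measure.

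Three stronger readings are tempting and are not supported:

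- That safety cannot be compared between arms at all. The shared parent rating and the blinded SR and %SS allow a plateau to be derived alike in every arm at the scheduled points.
- That LP will look less safe. The direction of any bias is undetermined.
- That the distortion can be expressed in events. The complement of the 80% maintained near-zero stuttering expected in 11.4.2 might seem to give a rate of 20%. But a child who improves to mild stuttering falls in that 20% without having a plateau event, and no detection probability has a source in the protocol.

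The consequence falls on the periodic safety review and on descriptive reporting by arm. No effect on the primary analysis has been shown. The conclusion assumes that the safety documents not seen do not already fix a common measure.

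**What to change.** In sections 10.2 to 10.4, and in the safety analysis of 11.3.3, name one measure collected identically in all arms for ascertaining this event.

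- **By-arm safety table.** Derive lack of reduction from baseline from the blinded SR and %SS at the scheduled data collection points, with the scheduled parent rating as support. Make this the main between-arm comparison. List SLT-reported events separately, with a note that ascertainment was unequal.
- **Alert during the trial.** A REDCap prompt based on the scheduled parent rating may ask the SLT and Co-CI to review a child. The criterion is for the investigators to set and must be reconciled with the protocol's own event definition. The severity bands in 8.9.3 were written for video analysts, and a single parent rating of stuttering today is not a 10-week plateau.
- **Spontaneous SLT reports** continue as now.

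The cost is a wording amendment and one optional alert on a variable already collected. The downsides are some false prompts and first detection at about week 11 to 15 rather than 10. Some bias also remains in the parent rating, because parents are unblinded and LP parents are trained in rating. That is why the blinded scores should carry the comparison.

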## 10.5 Notification of deaths

Deaths will be notified to the Ethics Committee. However, these are extremely unlikely to be linked to this trial.

## 10.6 Reporting urgent safety measures

If any urgent safety measures are taken, Thomas More Mechelen-Antwerpen will immediately and in any event no later than 3 days from the date the measures are taken give written notice to KCE and the relevant EC of the measures taken and the circumstances giving rise to those measures.

## 10.7 The type and duration of the follow-up of subjects after adverse events

The decision can be (1) individualise the treatment to the PCWS's needs (2) leave the allocated treatment arm or (3) discontinuation of TreatPaCS. The first action can include a variety of measurements. The duration of the follow-up depends on the action that was taken and will be specified by the Trial Management Group but takes at least 6 weeks.

# 11 STATISTICS AND DATA ANALYSIS

Thomas More Mechelen-Antwerpen assigned the statistical analysis to CTC UZ-ANTWERPEN.

The details of the statistical analysis will be described in a separate statistical analysis plan which will be finalised before data base lock.

## 11.1 Sample size calculation

In this trial the aim is to prove non-inferiority of Mini-KIDS compared to LP and SCBT compared to LP. The primary outcome is %SS at 18 months post-randomisation.

The non-inferiority margin was set at 1.0% SS following Bridgeman et al. (2016) and Donaghy et al. (2020). Several studies report a standard deviation on %SS at 18 months varying from 0.4 to 2.1 in different number of children (Arnott et al. 2014; Bridgeman et al. 2016; Donaghy et al. 2020; De Sonnevile-Koedoot et al. 2015). Pooling all these results (weighing them with the number of children per study) we estimated a value of 1.7 for the standard deviation at 18 months on %SS. We adjust the usual one-sided significance level of 2.5% to 1.25% because we are interested in the two comparisons (Mini-KIDS versus LP and SCBT versus LP).

Assuming that in reality there is no difference between the three programs and using a power of 90% and a one-sided significance level of 1.25% we need 73 children in each group to show non-inferiority. Taking into account a 11% dropout (de Sonnevile-Koedoot et al. 2015) we need to randomise 249 children in total (83 children per arm).

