A meta-analysis of two clinical trials (Jones et al., 2005; Lewis et al., 2008) and two clinical experiments (Lattermann et al., 2005; Harris et al., 2002) conducted with the LP (Onslow et al., 2012) involved 134 children. The children in the control groups received the LP after 9 months of no treatment; it would be unethical to deny them of any treatment. At pre-randomisation the stuttering severity of the group who received the LP and the control group were about the same. There was a small average improvement in the control group over time due to spontaneous recovery, which was predictable (Onslow, 2021). However, at a mean post-randomisation period of 6.3 months, the group who received the LP did significantly better than the control group. The LP odds ratio at that point in time was 7.5 for achieving %SS of below 1.0. So, the children who received the LP had 7.5 times greater odds of having “no stuttering” or “almost no stuttering” than children who did not receive the LP.

SCBT contains five treatment phases: (1) conditioning speaking activities, (2) cognitive training focused on emotions, (3) cognitive training focused on cognitions, (4) desensitisation (emotional training) and (5) skill training (Boey, 2010). This treatment is not directed at the speech of the children, but rather at the cognitive and emotional aspects that surround the stuttering. Boey (2008) published a study on the long-term effect of SCBT in different age groups as part of his dissertation.

Mini-KIDS is a direct treatment based on principles of stuttering modification through pseudo-stuttering, that is, deliberate stuttering, as one of the main components. The program for 4-6-year old children consists of four stages: Stage 1 = desensitization, Stage 2 = identification, Stage 3 = modification and Stage 4 = generalization. The program for 2-4-year old children does not include stage 2. SLTs and parent(s) are the speech model for the child. They add normal dysfluencies to their speech. Later on in treatment and if necessary, children learn to recognise and alter their stuttering moments.

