## 4.3 Endpoints

### 4.3.1 Primary endpoint

The primary endpoint is %SS at 18 months post-randomisation. %SS is measured by the blinded video analysts on video recorded speech samples from home and from the treatment session and will be computed as the average of the two speech samples.

For stuttering, no core set of measurements exist. %SS was chosen as it is the most frequently used objective measure in clinical trials that compares stuttering treatment. It is used in universally known stuttering severity instruments (e.g., SSI-4). A similar measure on word level is used in locally administered stuttering severity instruments (e.g., TVS-NL, TSB-NL).

The taxonomy of Teesson et al. (2003, p. 1008) can be used to categorise the stuttered syllables:

[figure not shown]

Figure 2. Taxonomy of Teeson et al. (2003) to classify stuttered syllables

Fixed postures with audible airflow are often referred to as prolongations; fixed postures without audible airflow are often referred to as blocks.

The 18-months post-randomisation time point was chosen to enable all participants to complete the treatment phase and achieve the goals of each treatment approach. The median number of treatment sessions, calculated in 30 minutes, are expected to differ. For the LP, it is expected to be 47, for Mini-KIDS 61 and for SCBT 94 (for SCBT treatment sessions are scheduled two times a week). These numbers of treatment sessions include the screening session, the parent coaching session(s) or parent training, the treatment phase and the maintenance phase, which is scheduled after the treatment goals were achieved to monitor the stuttering on the long term as stuttering is known to be a relapse-prone disorder.

A similar RCT conducted in the Netherlands in which the LP was compared to Restart-DCM, used the same primary endpoint (De Sonnevle-Koedoot et al., 2015). Restart-DCM is an indirect treatment program for PCWS that is delivered frequently in the Netherlands. More RCTs with the LP used 18 months post-randomisation as data collection point: Donaghy et al. (2020) who compared the LP with and without verbal

contingencies, Bridgman et al. (2016) who compared the LP delivered in the clinical practice with the LP delivered via webcam, and Arnott et al. (2014) who compared the LP with the LP in group format.

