### 8.9.3 Video analysis: Rating of %SS and SR

The video analyst coordinator organises the video analysis process. The video analysts look at the videos that are uploaded onto a GDPR-proof platform to calculate %SS and assign a SR to the two video recordings (one from home and one from the treatment session) at each data collection point. An average of the two scores will be taken as outcome measure. Success of the intervention is frequently defined in terms of achieving <1% SS. To achieve such a low average, one must have very low scores in both speech samples (home and during the treatment sessions), so averaging the % SS is routine practice in the standard clinical care.

The video analysts will be able to access the video recordings without knowing which treatment approach the PCWS is receiving/has received. A list of the videos of the French-speaking PCWS (for the French-speaking video analysts) and a list of the videos of the Dutch-speaking PCWS (for the Dutch-speaking video analysts) will be generated without information about the treatment arm and the time on which the video is recorded. In each list, 5% of the video recordings will re-appear as those are intended to be rated by two video analysts to establish the interrater agreement (see further for detail about the interrater agreement analysis). This 10% of videos is clearly indicated on the list. The video analysis will commence 6 months after the start of recruitment. This 6-month waiting time is included to avoid bias for the baseline video recordings.

If a PCWS speaks another language than Dutch, French or English, the research team will use their network to search for a native speaker of the language spoken by the PCWS and parent. This person will be invited to help the video analyst with scoring the video.

Standardisation of the video analysts will be guaranteed by a manual and by a training in which three video recorded speech samples (other than TreatPaCS-videos) will be scored together with all video analysts for %SS and SR.

Quality of the ratings will be assured by an evaluation of five video samples of French-speaking PCWS performed by the French-speaking video analysts and five video samples of Dutch-speaking PCWS performed by the Dutch-speaking video analysts. In a meeting they will discuss the stuttering moments and come to a consensus.

For %SS, clear instructions will be provided, including:

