#### *11.4.2 Potential effects on health*

Potential effects on health from the intervention on the QOL-measures (EQ-5D-5L proxy 1) are expected to be visible in increased QOL-scores due to increased fluency. In this QOL-instrument, the subscales of “Doing usual activities” and “Feeling worried, sad or unhappy” are the ones of interest.

The estimated outcome in the comparator arm (LP) is “no problems doing the usual activities” and “being not worried, sad or unhappy” in 95% of the children 2 years post-randomisation and in 85% of the children 5 years post-randomisation. The estimated outcome in the experimental treatment arms (Mini-KIDS and SCBT) is also “no problems doing the usual activities” and “not worried, sad or unhappy” in 95% of the children 2 years post-randomisation and in 85% of the children 5 years post-randomisation.

The estimated outcome in the comparator arm (LP) is (near) zero stuttering levels that are maintained in 80% of the children at 2 and 5 years post-randomisation. The estimated outcome in the experimental treatment arms (Mini-KIDS and SCBT) is also (near) zero stuttering levels that are maintained in 80% of the children at 2 and 5 years post-randomisation.

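### The 1.0 %SS margin rests on precedent from Lidcombe-variant trials and is not tied to a tolerable loss of success, and success gets no pairwise interval against LP

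*Protocol*

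**What the plan says.** Section 11.1 of the protocol: "The non-inferiority margin was set at 1.0% SS". The only reason given is that two earlier trials used it. Section 4.3.1 describes these two: one is the trial "who compared the LP delivered in the clinical practice with the LP delivered via webcam", the other compared LP with and without verbal contingencies. The same section 11.1 reports "we estimated a value of 1.7 for the standard deviation at 18 months on %SS", a one-sided level of 1.25% per comparison, 90% power at no true difference, and 73 children per arm (249 randomised).

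On success, section 8.9.3 says "Success of the intervention is frequently defined in terms of achieving <1% SS". Sections 4.2, 4.3.2 and 11.3.3 define a successful child as below 1 %SS with a severity rating (SR) of at most 1. Section 11.3.3 says of the success proportions at 18 months and 5 years: "They will be compared by a Chi-square test (or Fisher's exact test as appropriate) between the three programs". It adds a Kaplan-Meier plot and an adjusted Cox model for time to success. Section 11.3.5 adds an exploratory logistic model with success as outcome, to look for child profiles.

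The evidence for LP against no treatment, in section 1, is on the success scale: "The LP odds ratio at that point in time was 7.5 for achieving %SS of below 1.0". Section 2 expects the three programs to reach a similar outcome at 18 months, meaning near-zero stuttering. Section 11.4.2 puts the maintained near-zero rate at 80% in every arm at 2 and 5 years.

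**The concern.** The outcome the trial hopes to show as similar is a proportion of children at near-zero stuttering, while the primary test is on a mean. A margin on the mean says something about that proportion only if someone has worked out what loss of success it allows, and the protocol does not do this. The precedent comes from comparisons of LP with another form of LP. Here the margin is applied to two different programs which, by section 3, are not evidence-based as wholes.

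The success analysis does not close the gap. An omnibus test across three groups does not say which program differs from LP or by how much, and failing to reject it is no evidence of similarity. At stake is a report that a program is non-inferior, beside a non-significant success test, when the data do not exclude a sizeable loss of successful children.

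**Working it through.** **1. The plan's own figure.** Inputs from section 11.1: margin 1.0, SD 1.7, one-sided level 1.25% (z = 2.2414), power 90% (z = 1.2816), true difference 0.

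n = (2.2414 + 1.2816)² × 2 × 1.7² / 1.0² = 71.7, so 72 per arm by the normal approximation. The t distribution gives 73 (power 0.900). With 11% dropout, 73 / 0.89 = 82.02, so 83 per arm and 249 in total. The stated size reproduces.

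**2. What the decision rule accepts.** SE = 1.7 × √(2/73) = 0.2814. The upper limit of the two-sided 97.5% interval lies below 1.0 when the observed excess is below 1 − 2.2414 × 0.2814 = 0.37 %SS (0.36 by t). The chance of declaring non-inferiority, by true mean excess:

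| True excess (%SS) | 0 | 0.3 | 0.4 | 0.5 | 1.0 |
|---|---|---|---|---|---|
| P(non-inferior) | 0.90 | 0.59 | 0.45 | 0.32 | 0.012 |

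**3. From mean to success.** The protocol gives no 18-month success rate and no distribution. Assumptions: 60 to 80% of LP children below 1 %SS (80% is the protocol's figure for 2 and 5 years), and gamma or lognormal scores with SD 1.7 in LP. 73 per arm, 20,000 simulated trials per case, unweighted comparison of means.

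*Case A: SD 1.7 in both arms, as the sample size assumes.* The second column is the mean excess that corresponds to the lower success rate.

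| Fewer children below 1 %SS | Mean excess | P(non-inferior) |
|---|---|---|
| 15 points | 0.33–0.41 | 46–62% |
| 20 points | 0.44–0.54 | 28–46% |

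*Case B: the worse arm's scores are scaled up, so its spread grows with its mean.*

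| Fewer children below 1 %SS | SD in worse arm | P(non-inferior), gamma | P(non-inferior), lognormal |
|---|---|---|---|
| 15 points | 2.5–5.6 | 0–1% | 23–24% |
| 20 points | 2.8–8.5 | 0% | 6–8% |

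**4. The three-group Chi-square at 5%.** Power by simulation; rates are LP / second program / worst program.

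| Success rates (%) | 73 per arm | 83 per arm |
|---|---|---|
| 80 / 80 / 65 | 56% | 62% |
| 80 / 65 / 65 | 53% | 59% |
| 80 / 72.5 / 65 | 43% | 48% |
| 80 / 80 / 60 | 81% | 85% |
| 80 / 60 / 60 | 78% | 84% |

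With 60% success in LP, 73 per arm and one worse program, power is about 45% for a 15-point loss and 72% for 20 points.

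**5. Both results together.** Under case A with LP at 80% and one program 15 points worse, about 31 to 34% of trials declare that program non-inferior and also return a non-significant Chi-square.

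**6. What a pairwise interval would show.** The 97.5% half-width for a success difference with 73 per arm is 2.2414 × √((0.80 × 0.20 + 0.80 × 0.20)/73) = 14.8 points at equal 80% rates. It is 16.3 points for 80% against 65%, and about 18 points if both rates are 60%.

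**The case against.** Several stronger readings are tempting, and the protocol does not support them.

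- **That the Chi-square is the only success analysis.** It is not: a Cox model for time to success and an exploratory logistic model are also planned. Neither is specified as a pairwise difference in 18-month success with an interval.
- **That the Chi-square cannot detect such a loss.** With LP at 80% it detects a 15-point loss roughly half the time and a 20-point loss about 78 to 85% of the time.
- **That the plan tolerates a 15 to 20 point loss.** No such figure is in the protocol. It depends on an assumed LP success rate, an assumed distribution and equal spread. For skewed, non-negative scores a worse arm may well be more variable, and the pass rate then drops sharply.
- **That a program 1.0 %SS worse for every child would be accepted.** The test passes it only 1.25% of the time.
- **That the margin is nearly the whole LP effect.** That would carry an odds ratio observed at a mean of 6.3 months to 18 months, and turn it into means through an assumed distribution. The protocol gives no mean effect of LP over no treatment.

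A fair opponent would add that LP-variant trials are not automatically a poor precedent, and that their own reasons for 1.0 cannot be seen here. The opponent would also say that pairwise intervals are a detail for the SAP, and that they detect a loss no better. On detection the opponent is right: a 97.5% interval lies wholly below zero for a true 15-point loss (80% against 65%) only about 42% of the time, against 56% for the Chi-square when one arm is worse. That argues against making such an interval a condition for the non-inferiority label. It does not argue against reporting it, because its purpose is to show which program differs from LP and what loss is not excluded. Nor is this only a matter left to the SAP: section 11.3.3 itself names the omnibus test.

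**Conclusion.** The point holds as a cheap improvement to the plan; the sample size and the primary test are not in error. Three things follow from the document alone: the margin is justified only by precedent from LP-variant trials, it coincides with the %SS success cut-off without being tied to a tolerable loss of success, and the named test of success proportions gives no pairwise difference from LP with an interval.

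The size depends on assumptions. The pass rates under equal spread are appreciable and use the protocol's own SD, but they become small or nil if the worse arm is more variable. They cover only the %SS part of success, since SR could not be modelled. They also ignore the planned inverse probability weighting, which would widen the primary interval and lower the pass rates. What does not depend on these assumptions is that a non-significant three-group test is not evidence of similar success.

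**What to change.** Keep the sample size, the 1.0 %SS margin and the primary test.

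- **Section 11.3.3:** replace or supplement the Chi-square on 18-month success with two pairwise differences in success proportion, Mini-KIDS minus LP and SCBT minus LP. Give each a two-sided 97.5% confidence interval, in both the intention-to-treat and the per-protocol populations, and report them beside the primary result. State that a non-significant test is not to be taken as evidence of similar success.
- **Section 11.1:** add a sentence saying that 1.0 %SS was adopted by precedent, equals the %SS success cut-off, and was not derived from a tolerable loss of success.

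The cost is wording and two intervals per population, from data already collected. Section 11 says the SAP will be finalised before database lock, so this can be fixed before results are known. The downside is that a half-width of about 15 to 16 points (about 18 if success is near 60%) will show plainly how large a loss remains possible, so a claim of similar success may look less favourable.
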